##### Investigation for cost data

In the healthcare field, cost items can be categorized into medical costs, non-medical costs, and costs from productivity loss [26–28]. Medical cost refers to expenses spent in using services at medical institutions (direct medical costs) and unofficial expenses spent in buying health products or medical devices (indirect medical costs). Non-medical costs include costs accompanied in medical service use such as transportation fees, patient time, and caregiver expenses. Cost of productivity loss is the cost of economic losses from not being able to participate in labor due to the disease itself or premature death from disease. The Work Productivity and Activity Impairment questionnaire (WPAI) will be used to calculate the cost of productivity loss and it will be applied for cost–utility analysis.

##### Credibility and Expectancy Questionnaire

The Credibility and Expectancy Questionnaire [29], which consists of a 9-point Likert scale, will be used for the evaluation of participants’ expectations towards treatment. On the first visit of week 1 (visit 2), participants will choose the score that best answers the following question (1 = not at all, 5 = somewhat, and 9 = very much): “How much do you expect the treatment(s) you will receive during the study period to improve your symptoms?”

##### Drug consumption

All medications taken over the study period as rescue medication or prescribed for treatment of the current complaint and their dosage will be recorded through surveys conducted on participant visits. Other physical therapies or injection therapies will also be recorded as the number of treatment sessions.

### Sample size

Calculation of number of participants required for the clinical trial: for calculation of significant number of participants, the following is hypothesized based on the previous literature:Level of significance, α = 0.05;Type II error (β) is set at 0.2 with power of the test set at 80%;According to a previous clinical study using VAS as the main assessment tool for Chuna manual therapy in neck pain patients, the effect size of Chuna manual therapy in comparison to the control can be considered to be 1.03 [30], and 1.49 [31], respectively;Compliance rate will be set at 85% (the predicted rate of receiving ≥ 6 sessions of treatment during the five-week treatment period);For calculation of sample size, G*Power 3.1.7 was used. With evidence from item (3), application of mean ± SD resulted in conservatively hypothesizing the effect size of this clinical trial as 0.6 because of the high clinical heterogeneity of manual therapies such as Chuna. Application of items (1) and (2) and the effect size resulted in the calculation of a sample size of 90 participants (45 in each group).The mean comparison of pain requires a total of 90 participants (45 in each group), which is the minimum number of participants needed for testing the abovementioned hypothesis. Considering that 15% of participants received < 6 sessions of treatment within the five-week treatment period, a total of 108 participants, 54 in each group, will be extracted for the study.

### Statistical analysis

The main evaluation method will be by intention-to-treat (ITT) analysis that evaluates participants who received at least one session of treatment. Per-protocol (PP) analysis will also be performed, which analyzes only participants who complete participation in the clinical trial in the initial allocated group, excluding participants who withdrew or crossed over during the study. Missing values will be processed mainly by multiple imputation, and last observation carried forward (LOCF) will be used for sensitivity analysis. Participants who received ≥ 6 sessions of treatment during the five-week treatment period will be analyzed separately.

The sociodemographic characteristics and treatment expectancy of participants will be evaluated by group. Continuous variables will be presented as average (standard deviation) or median values (quartile), and the two groups will be compared using Student’s t-test. Wilcoxon rank-sum test will be conducted if the data do not follow normal distribution. Categorical variables will be presented as frequency values (%), and Chi-square test or Fisher’s exact test will be performed as appropriate.

The efficacy variable for this clinical trial is the difference in continuous outcomes (i.e. NRS, VAS, NDI, NPQ, EQ-5D-5 L, SF-12) between baseline and predetermined timepoints. The primary endpoint is one week after completion of treatment (seven weeks after random allocation). Baseline values of each outcome and covariant factors which show statistical difference between groups at baseline will be set as covariates, and analysis of covariance (ANCOVA) with the treatment groups designated as the fixed factor. In addition, to examine the trend difference by visit, repeated measure (RM) ANCOVA will be performed.

To compare the total difference in outcome between the two groups within the treatment period (six weeks) and total study period (one year), the area under the curve (AUC) by specific timepoint after random allocation will be calculated and compared using the Student’s t-test.

Specific timepoints where the VAS and NRS fall under the half line point of the baseline standard will be performed for a comparative analysis on patient improvement rate. To measure the time between random allocation to the point when neck pain improves to less than half the original pain intensity, Kaplan–Meier survival analysis will be used for analysis and the curve will be compared using the log-rank test. A Cox model will be used to calculate the hazard ratio to compare the speed at which pain improves to less than half the original pain. Whether the recovery speed differs by subgroup will also be examined.

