### Randomization and allocation concealment

Stratified block randomization will be conducted with stratification by each study site to help control for potential bias in the control and experimental groups. Upon randomization within each study site, participants will be allocated to either the control or experimental group according to the allocation code, and the number of participants in each group will be identical between groups for all study sites.

Random allocation will be performed by a statistician by randomly allocating 54 participants to each group under the condition where the possibility of being chosen is identical for all individuals using SAS version 9.4 statistical package (SAS institute, Cary, NC, USA). The number of participants for each study site will be 24 for Jaseng Hospital of Korean medicine Gangnam branch, 22, respectively for Jaseng Hospital of Korean medicine Bucheon, Daejeon, and Haeundae branches, and 18 for Kyunghee University Korean medicine Hospital at Gangdong. The results of random allocation will each be sealed in opaque envelopes before being sent to each study site and will be kept stored in double lock cabinets.

The researchers responsible for registration of eligible participants at each study site will fully explain to the participants about the clinical trial before receiving written informed consent from the participants. The coordinators will assign randomized numbers by the sequence of registration to participants to be included in the clinical trial following the inclusion/exclusion criteria who will thus be allocated to either one of the two groups at a 1:1 ratio by opening the sealed envelope in front of the participant. The opened envelopes will be kept separately in a double-lock cabinet. The randomized numbers allocated to each participant will be recorded in the electronic medical chart records.

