### Blinding

Since it is not feasible to double-blind the practitioner and participant regarding allocation to the two types of treatment due to the study design, blinding of the outcome assessors and statistician will be performed. The outcome assessor will not partake in treatment and a clinical research nurse or a Korean medicine doctor blinded to group allocation will evaluate the participant in a separate area before treatment, and will not try to guess the treatment allocation group to which the participant may be allocated. Computerized data passed on to the statistician will not contain any information identifying patient allocation to either of the two groups.

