#### Subgroup analysis

Sociodemographic characteristics: body mass index, age (≥ 40 years; and < 40 years), sex, recommendations for surgery, driving, headache, depression, number of sick leave days from work;Physical examination: neurologic examination (sensory loss, muscle weakness), pain upon range of motion (ROM) (i.e. flexion, extension, lateral bending, rotation);Pain characteristics: area of neck pain (bilateral/unilateral, central/trapezius/back), existence of radiating pain (yes/no, unilateral/bilateral, pain under the elbow joint, pain in the back), pain characteristics (acute onset versus slow onset, persistent versus aggravating), conditions of pain aggravation (understress, fatigue), nocturnal pain;Treatment prior to study: experience of Chuna manual therapy, continuation of physical therapy or conventional medication;Expectancy and preference for treatment: credibility and expectancy, preference (Chuna manual therapy; usual care; or no preference);X-ray examination: head forward posture, lateral deviation of spine, cervical intervertebral disc space, degenerative change;Index severity evaluation: VAS ≥ 7 and < 7, NDI high/low.

All statistical analyses were performed with SAS version 9.4 statistical package (SAS Institute, Cary, NC, USA), with the level of significance set at *p* < 0.05.

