### Stopping rules

It will be noted whether study participants completed the study; when treatment or observation is suspended, the reason will also be recorded. For participants who have been suspended from study, follow-up observations may be continued with the participant’s consent. Circumstances that disable further continuation of study participation include SAEs, detection of disease(s) that may potentially affect the study results, and withdrawal of participant consent for study participation.

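### The main analysis is labelled ITT but keeps only participants who had at least one session, so this open-label trial states no analysis of everyone randomized

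*Protocol article*

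**What the plan says.** The Statistical analysis section names the main evaluation as an "intention-to-treat (ITT) analysis that evaluates participants who received at least one session of treatment". It adds a per-protocol analysis, "excluding participants who withdrew or crossed over during the study", and a separate analysis of those with six or more sessions. On missing data it states: "Missing values will be processed mainly by multiple imputation, and last observation carried forward (LOCF) will be used for sensitivity analysis".

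Under Randomization and allocation concealment, participants learn their arm "by opening the sealed envelope in front of the participant". The Blinding section explains why only the outcome assessor and statistician are masked: "Since it is not feasible to double-blind the practitioner and participant regarding allocation to the two types of treatment". The Subgroup analysis section lists "preference (Chuna manual therapy; usual care; or no preference" among its factors, so the investigators expect that some participants will favour one arm.

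For participants suspended from the study, the Stopping rules section says that "follow-up observations may be continued", subject to consent.

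**The concern.** Intention-to-treat means everyone randomized, analysed in the arm to which they were allocated. A rule that requires one session selects on a post-randomization event. In a double-blind trial this can often be defended, because a hidden allocation cannot influence who starts. That defence is not available here. The participant knows the arm before any treatment, may have come to a Korean medicine hospital hoping for Chuna, and under Co-interventions agrees to no other pain treatment during the treatment phase. Someone who draws the less wanted arm could decline at that point.

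If refusals are uneven between arms and the decliners would have reported different pain from those who stay, the retained groups are no longer the randomized groups. Baseline adjustment cannot be relied on to restore the balance. The outcome is self-reported pain in an unblinded trial, so a link between preference and outcome is plausible, although the article does not demonstrate one.

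**Working it through.** **1. The plan's own sample size.** Inputs from the Sample size section: alpha 0.05, power 80%, effect size 0.6, 15% allowance for fewer than six sessions. The section does not say whether the test is two-sided, but a two-sided two-sample t-test needs 45 per arm (power 0.804), which matches the stated 90; a one-sided normal approximation gives 35 and does not match. Inflation: 45 / (1 − 0.15) = 52.9, so 53 per arm or 106, against the stated 54 per arm or 108. The figure reproduces closely and is not at issue. With all 108 analysed (54 v 54), power at 0.6 SD is 0.871 if the full effect is kept.

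**2. The analysis sets side by side.**
- Main set: at least one session.
- Per-protocol: completed in the allocated arm, without withdrawal or crossover.
- Separate analysis: at least six sessions.

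A participant with no session belongs to none of them. The planned multiple imputation therefore never reaches that person.

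**3. The room for loss between allocation and first session.** The article gives two incompatible timings.
- The Abstract puts the primary outcome 5 weeks after randomization, and Primary outcome measurement puts it five weeks after visit 2, where baseline VAS is taken. Together these imply randomization at visit 2. Trial design and study setting starts treatment from the second visit, so the gap is about zero.
- Statistical analysis puts the endpoint one week after the end of treatment and seven weeks after allocation. With five weeks of treatment, 7 − 1 − 5 = 1 week between allocation and the first session.

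**4. Size of the shift.** Let k of the 54 in one arm have no session, and let their mean outcome differ by g SD from that of the retained 54 − k. The full-arm mean is the retained mean plus (k/54)g, so dropping them moves the arm contrast by (k/54)g. Neither k nor g is documented. The values below are assumptions.

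| k | g = 0.25 | g = 0.5 | g = 1.0 |
|---|---|---|---|
| 1 | 0.005 | 0.009 | 0.019 |
| 3 | 0.014 | 0.028 | 0.056 |
| 5 | 0.023 | 0.046 | 0.093 |
| 8 | 0.037 | 0.074 | 0.148 |

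As a share of the planned 0.6 SD, this runs from 0.005/0.6 = 0.8% to 0.148/0.6 = 24.7%. If the true effect is zero, the two-sided type I error of a t-test (54 v 54 − k) goes from 0.0501 at the smallest corner to 0.113 at the largest.

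**5. How plausible the top of the range is.** k = 8 is 8/54 = 14.8% of one arm. That is about the plan's whole 15% allowance for fewer than six sessions, which also covers everyone who attended one to five. The largest figures are therefore an outer bound.

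**6. What imputation alone would do.** If decliners are added back with no outcome and imputed at random from arm and baseline, their imputed mean follows that of comparable retained participants. The estimate then stays close to the one without them, and most of (k/54)g remains. Observed outcomes, or predictors related to both declining and pain, are needed to reduce it.

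**The case against.** The best defence is the visit structure. If the envelope, the baseline VAS and the first session all fall at visit 2, there is little opportunity to leave, and the at-least-one-session set may be almost everyone randomized. Participants also consent after a full explanation, so they accept either arm in advance. Both points limit the likely size. They do not rescue the label: refusal on the spot remains possible, and the seven-week timing suggests a gap. It is also true that someone who never attends visit 2 has no baseline VAS, so one cannot assume both a long gap and complete baseline data.

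Some stronger readings are tempting but not supported.
- A reader might infer an as-treated analysis. Nothing says that participants are regrouped by treatment received; treatment group is the fixed factor, and crossovers are excluded only from the per-protocol set.
- A reader might infer that randomization is broken. That is a conditional risk, and the article gives no number of decliners, no imbalance between arms and no direction.
- A reader might fault the choice of LOCF or the lack of a tipping-point analysis. LOCF is only the sensitivity method here, and further sensitivity detail is commonly left to an analysis plan that is not shown.
- The Stopping rules wording already rests on consent and concerns suspended participants. It is not a separate fault, but it shows that outcome collection after stopping is permitted rather than expected.

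**Conclusion.** The point holds as a matter of definition: the set called ITT is a modified ITT set, and the article states no analysis of all randomized participants. This can be said with confidence from the text. Because allocation is known before treatment starts, the main comparison lacks the guarantee that ITT is meant to give.

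The bias itself is not established. It is about 0.005 to 0.15 SD if 1 to 8 of 54 in one arm decline and differ by 0.25 to 1.0 SD, all of which is assumed, and it is near zero if allocation and first session coincide. Its direction cannot be determined from the documents.

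**What to change.** - Define the primary analysis set as all randomized participants, analysed in the arm to which they were allocated.
- State that week-5 VAS will be sought from everyone who consents to follow-up, including those who never start treatment. This step does most to reduce the bias.
- Handle the remaining missing values by the multiple imputation already planned, with screening and baseline data as predictors: NRS and, where recorded, preference and expectancy. Screening NRS matters for anyone who leaves before visit 2, when baseline VAS is taken.
- Keep the at-least-one-session set as a sensitivity analysis, labelled modified ITT.
- Report by arm how many were randomized but had no session, and reconcile the timing of the primary endpoint relative to allocation, so that readers can judge the window for loss.

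The cost is a wording change and slightly more follow-up and imputation work. The sample size of 108 stands.

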**Methods/Design:**

This study is the protocol for a two-armed parallel, assessor-blinded, multicenter, randomized controlled trial. A total 108 patients with chronic neck pain (time to onset ≥ 3 months, numeric rating scale [NRS] of neck pain ≥ 5) will be recruited at five Korean medicine hospital sites. Participants will be allotted to one of two groups (*n* = 54, respectively): the Chuna manual therapy group, and the usual care (conventional physical therapy and medication treatment) group. Ten sessions of Chuna manual therapy or usual care will be administered twice a week for five weeks. Since the study design does not permit patient or physician blinding, the outcome assessor and statistician will be blinded. The primary outcome will be the visual analogue scale (VAS) of neck pain at 5 weeks after randomization. Secondary outcomes include the VAS of radiating arm pain, NRS of neck pain and radiating arm pain, Vernon-Mior neck disability index (NDI), Northwick Park neck pain questionnaire (NPQ), EuroQol-5 Dimension (EQ-5D), EQ-VAS, patient global impression of change (PGIC), economic evaluation, adverse effects, and drug consumption. Follow-up outcome assessments will be conducted at 3, 6, 9, and 12 months after randomization.

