#### Co-interventions

No additional treatment (Korean medicine treatment, conventional medicine medication or procedures, physical or exercise therapy) to the purpose of relieving pain other than the treatment provided in the study will be allowed over the course of treatment until the sixth week which is the primary endpoint. However, the research will set no limits after the sixth week. In case the participants in the experimental or control groups experience severe pain during the study period, administration of acetaminophen (maximum dosage of 4 g per day) will be allowed as a rescue medication due to ethical issues. Its use will be specifically reflected and assessed in describing outcomes in the results paper.

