### Outcomes

#### Primary outcome measurement

The primary outcome will be the visual analogue scale (VAS) of the past three days’ neck pain. VAS refers to an evaluation tool that records the degree of pain the patient feels with one end indicating no pain and the other end indicating the most severe pain imaginable on a 100 mm line [18, 19]. Participants will be asked to mark the one point that best describes his or her neck pain during the previous week.

The difference in VAS at baseline (visit 2) and the primary endpoint (follow-up 1 [visit 11]: five weeks after visit 2) will be used to compare the two groups to identify the difference in effect size.

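### The per-protocol set has no cut-off at the primary endpoint, so later drop-out, and possibly permitted later treatment, can remove valid endpoint data from the per-protocol comparison

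*Protocol article*

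**What the plan says.** The Statistical analysis section makes intention-to-treat (ITT), in participants with at least one session, the main analysis and adds a PP analysis. The PP analysis "analyzes only participants who complete participation in the clinical trial in the initial allocated group", "excluding participants who withdrew or crossed over during the study". No time limit is attached. The same section speaks of the "total study period (one year") and, separately, plans an analysis of participants with six or more sessions in the five-week treatment period.

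The abstract states: "Follow-up outcome assessments will be conducted at 3, 6, 9, and 12 months after randomization". Under Co-interventions, other pain treatment is barred only up to week 6: "However, the research will set no limits after the sixth week".

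The primary endpoint has three times:
- Primary outcome measurement: "follow-up 1 [visit 11]: five weeks after visit 2"
- Co-interventions: "until the sixth week which is the primary endpoint"
- Statistical analysis: "The primary endpoint is one week after completion of treatment (seven weeks after random allocation")

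**The concern.** A PP analysis of a short-term endpoint should ask who followed the protocol up to that endpoint. This rule also looks at what happened in the following ten months or so. Someone who attended all ten sessions, gave a valid endpoint value and was lost at month 9 has not completed the trial and drops out of the set. Someone who took up the other arm's treatment at month 4, as the protocol allows, may drop out too.

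Two things are at stake. Valid endpoint data are discarded, which widens the PP interval. The set is also selected on events after the outcome was measured. If those events are related to the endpoint response, and arise to a different extent in the two arms, the PP difference is distorted. Agreement or disagreement with the ITT result then becomes harder to read.

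**Working it through.** **Yardstick from the plan.** The Sample size section gives effect size 0.6, alpha 0.05, power 80% and 45 per group, raised to 54. A two-sided two-sample t-test with these inputs needs 44.59, so 45 per arm (power 80.4%). Inflating for 15%: 90/0.85 = 105.9, so 106, against the stated 108. The figure reproduces and does not depend on the PP definition. The 15% covers fewer than six sessions in five weeks, not one-year withdrawal or crossover.

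**Text check.** The withdrawal part of the rule needs no interpretation: a month-9 drop-out has not completed the trial. The crossover part does, since the term is undefined. Where the section wanted a treatment-period window, as in the six-session analysis, it wrote one. The PP rule has none.

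**Precision.** The standard error grows by 1/√(1-p) when a proportion p is lost from each arm: 1.08 for p = 0.15 and 1.20 for p = 0.30. Power at effect size 0.6 is 87% with 54 per arm, 80% with 45, 75% with 40 and 70% with 35. The PP set falls below 45 per arm once more than 9 of 54 (16.7%) are lost in each arm.

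**Bias.** The documents give no rates or reasons for later withdrawal or crossover, so all rates here are assumptions. Model: endpoint improvement y is N(0,1) in usual care and N(0.6,1) in Chuna. The probability of later exclusion is 1/(1+exp(-(a - b·y))), with a set to give the assumed rate and b = 0.5 or 1 log-odds per SD, so that poorer responders leave more often. With 300,000 simulated participants per arm, the Monte Carlo standard error of the difference is about √(2/300,000) = 0.003 SD.

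| Excluded, usual care / Chuna | PP difference, b = 0.5 | b = 1 |
|---|---|---|
| 15% / 15% | 0.599 | 0.599 |
| 30% / 30% | 0.602 | 0.602 |
| 10% / 0% | 0.549 | 0.513 |
| 20% / 5% | 0.532 | 0.476 |
| 30% / 10% | 0.505 | 0.439 |
| 5% / 20% | 0.671 | 0.730 |
| 10% / 30% | 0.696 | 0.764 |

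With b = 0 (exclusion unrelated to response) every scenario stayed within 0.005 of the truth. When the same rule, with the same a and b, applied to both arms, 19% to 30% of usual care and 14% to 21% of Chuna were excluded, and the difference was 0.52 to 0.58. With no true effect, the unequal rates gave -0.163 to +0.161.

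The extremes are 0.439 - 0.6 = -0.161 and 0.764 - 0.6 = +0.164 SD, and 0.16/0.6 = 27%. For scale, at 30% / 10% loss from 54 per arm the standard error is about √(1/37.8 + 1/48.6) = 0.22 SD, so the largest bias is about three quarters of one standard error.

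**The case against.** The strongest objection is that the words can be read more narrowly. Allocated treatment lasts five weeks, so after week 6 there may be nothing left to cross over from. Care that the protocol permits need not count. The article also uses study period loosely: Economic evaluation sets it beside a follow-up period, and the Credibility and Expectancy Questionnaire item uses it where only the treatment weeks fit. The full protocol may define the terms. This stands as a reason not to assert that permitted treatment is crossover. It does not rescue the rule, because the wording does not secure the narrower meaning and the completion requirement catches late drop-outs anyway.

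It is also fair that PP is additional, that ITT with multiple imputation carries the primary comparison, and that the six-session analysis is an adherence analysis tied to the treatment weeks.

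A reader might infer more: that the rule strips poor responders from usual care and so shrinks the apparent Chuna effect. If only usual care loses participants, the shift in its mean is ρ·φ(z_p)/(1-p). With p = 0.3 and ρ = 0.7 this is 0.7 × 0.348/0.7 = 0.35 SD, or 58% of 0.6. The documents do not support that reading. It needs no loss at all in the Chuna arm, and neither the rate nor the correlation comes from the article. Recruitment at Korean medicine hospitals might ease a move to Chuna. However, usual care consists of the treatments most used in Korea, within a national insurance system that the Discussion says covers neck pain, so movement the other way is at least as conceivable.

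**Conclusion.** The point holds as a defect in a stated rule. The PP set for the primary endpoint is conditioned on events after that endpoint and, read literally, discards valid data from adherent participants. Loss of precision follows from any such exclusion. Bias in the contrast is possible but not established: it requires exclusion that depends on response and differs between arms, and its sign is unknown. Under the assumed rates it ranged from about -0.16 to +0.16 SD, at most about 27% of the planned 0.6, and was nil with equal exclusion rates and equal selection. Only the supplementary PP analysis is affected. Whether permitted later treatment counts as crossing over cannot be settled from the article.

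**What to change.** 1. Reconcile the primary-endpoint time across Primary outcome measurement (week 5), Co-interventions (week 6) and Statistical analysis (week 7), and with the end of the co-intervention restriction. Under the week-7 wording, unrestricted treatment begins before the endpoint, so a PP cut-off cannot be fixed until this is settled.
2. Define PP membership for the primary endpoint by withdrawal, crossover and prohibited co-treatment only up to the primary-endpoint assessment, and say what counts as crossing over.
3. State that later drop-out, and treatment permitted after the restriction ends, are not deviations for that analysis.
4. Define a separate PP set for the 3 to 12 month outcomes.

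The cost is a few sentences in the analysis-set definition and a text correction of the endpoint time. No new data, participants or visits are needed.

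### LOCF, the named sensitivity analysis, is an unreliable check on multiple imputation, and optional follow-up after withdrawal may add outcome-related missing data

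*Protocol article*

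**What the plan says.** In the protocol article, Statistical analysis: "Missing values will be processed mainly by multiple imputation", and "last observation carried forward (LOCF) will be used for sensitivity analysis". No other analysis that varies the missing-data assumption is named there.

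Two further analyses appear in the same section: a per-protocol analysis, "excluding participants who withdrew or crossed over during the study", and a separate analysis of those with six or more sessions. Both select people by completion or adherence. Neither asks how the missing people fared.

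Stopping rules: "Circumstances that disable further continuation of study participation include SAEs, detection of disease(s) that may potentially affect the study results", with consent withdrawal as the third listed reason. For those suspended, "follow-up observations may be continued with the participant"; the sentence goes on to make this depend on consent. Continued observation is thus allowed, but nothing says that it will be attempted.

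**The concern.** Multiple imputation in its standard form assumes that missingness is explained by the observed data (missing at random). The article does not state the assumption, but nothing suggests another. A sensitivity analysis should move that assumption in a known direction by a known amount. LOCF instead freezes each person at the last recorded value. Whether that helps or harms an arm depends on how many leave it and when.

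The trial gives reasons to care. Patients and practitioners are not blinded (Blinding), so leaving because of harm or lack of benefit could differ by arm. Two of the three listed reasons for ending participation, serious adverse events and detected disease, may be related to outcome.

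For the later outcomes the frozen value is hard to defend. The Abstract sets assessments at 3, 6, 9 and 12 months, and Co-interventions lifts all treatment limits after week six. The one-year area under the curve (Statistical analysis) and the QALYs (Economic evaluation) draw on those later values.

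**Working it through.** **Inputs from the article.** Effect size 0.6, 80% power and "Level of significance, α = 0.05" (Sample size); 54 per group; 15% expected to receive fewer than six sessions. That 15% is non-compliance. No rate of missing outcomes or of serious adverse events is given. The primary endpoint is taken at five weeks, as in the Abstract and the primary outcome section; the Statistical analysis section dates it differently, which does not affect this check.

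**The plan's own figure.** A two-sided two-sample t-test with d = 0.6, alpha 0.05 and power 0.80 needs 44.6, so 45 per group, matching the stated 90. Dividing by 0.85 gives 45/0.85 = 52.9, so 53 per group or 106; the stated 108 is within two. The point does not rest on a numerical error.

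**Step 1: what LOCF does.** Let c be the control-arm improvement in SD, and mT and mC the shares missing in the Chuna and control arms. Assume that leavers would have improved like the rest of their arm and that their last value is baseline. Then

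LOCF estimate = (1 − mT)(c + 0.6) − (1 − mC)c.

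| mT / mC | c = 0.5 | c = 1.0 | c = 1.5 |
|---|---|---|---|
| 15% / 15% | 0.51 | 0.51 | 0.51 |
| 15% / 5% | 0.46 | 0.41 | 0.36 |
| 5% / 15% | 0.62 | 0.67 | 0.72 |
| 5% / 25% | 0.67 | 0.77 | 0.87 |

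Example: 0.85 × 1.6 − 0.95 × 1.0 = 0.41. The same method shrinks or inflates 0.6 according to which arm loses more.

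**Step 2: agreement can be accidental.** The formula rearranges to 0.6 − 0.6·mT + c(mC − mT). With c = 1.0 this equals 0.6 whenever mC = 1.6·mT. Take mT = 10% and mC = 16%: 0.90 × 1.6 − 0.84 × 1.0 = 1.44 − 0.84 = 0.60. LOCF and multiple imputation would then agree exactly. If the missing Chuna participants were in truth 1 SD worse than imputed, the true effect would be 0.6 − 0.10 × 1 = 0.50. The agreement would say nothing about that.

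**Step 3: size on the primary result.** If a share m of the Chuna arm is missing and those people are truly delta SD worse than imputed, with control leavers as imputed, the bias is m × delta.

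- 3 of 54 (5.6%), delta 0.5 to 1.5: 0.028 to 0.083 SD, or 5 to 14% of 0.6.
- 10%, delta 0.5 to 1.5: 0.05 to 0.15 SD.
- 15%, delta 0.5 to 1.5: 0.075 to 0.225 SD; the upper end leaves 0.375.

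**Step 4: tipping point.** With 54 per group the smallest significant difference is t(0.975; 106 df) × √(2/54) = 0.382 SD. From an estimate of 0.6 the margin is 0.218 SD, so the tipping delta is 0.218/m: about 10.9 SD at 2% missing, 4.4 at 5%, 3.9 at 3 of 54, 2.2 at 10% and 1.5 at 15%. This ignores the extra variance from imputation, so the true tipping values would be somewhat lower. A smaller observed effect would also leave less margin.

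**Step 5: later follow-up.** A week-5 value carried to 12 months is carried 52 − 5 = 47 weeks. This applies only to someone who misses all four later assessments. The article gives no figure from which a 12-month bias could be computed.

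**The case against.** Four stronger readings are tempting, and the document does not support them.

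- A reader might infer that neither analysis allows for a worse course in leavers. That is not so. Someone who leaves early is carried at or near baseline, which in improving arms is worse than a missing-at-random imputation. With heavier loss from Chuna, LOCF is the harsher analysis (0.41 against 0.6). The fault is that its direction and size are accidental.
- A reader might infer that the Stopping rules create outcome-related dropout. They allow continued observation with consent, so data are lost only where this is not taken up. That it will lapse is an inference.
- A reader might infer that the primary result is in danger. At 3 of 54 missing in one arm, those people would have to be about 3.9 SD worse than imputed to overturn a 0.6 SD result. The Background cites adverse effects in up to half of manipulation patients, but these are not described as serious and give no dropout rate.
- A reader might infer that LOCF is the sole planned check. The article is condensed, the analysis plan is not shown, and the text does not call LOCF the only one. It also does not say that LOCF will be applied to costs.

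The Adverse events section already asks for safety reporting until an event resolves, so safety follow-up needs no new wording here.

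What stands against the objection is that the article does more than stay silent. It chooses LOCF as the sensitivity analysis, and it words outcome follow-up as optional.

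**Conclusion.** The point holds as a weak choice that the article states and that is cheap to improve. LOCF is an unreliable check on multiple imputation. Under the assumed loss patterns with c = 1.0, a 0.6 SD effect becomes 0.41 to 0.51 SD or 0.67 to 0.77 SD depending on which arm loses more, and the two methods can agree while both are wrong. The weakness is greatest for the 12-month and area-under-the-curve outcomes, though its size there cannot be computed from the document.

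The optional follow-up wording may add outcome-related missingness. For the five-week primary result the effect is probably small, 0.03 to 0.08 SD at 3 of 54 missing, and it becomes material only at about 10 to 15% missing in one arm. The missing shares, the values of delta, the control improvement and the baseline last value are all assumptions.

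**What to change.** In Statistical analysis, state the missing-at-random assumption behind the multiple imputation, and replace or supplement LOCF with delta-adjusted multiple imputation. Worsen the imputed values in the Chuna arm alone, in the control arm alone and in both, raising the shift until the conclusion changes, and report that tipping point.

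A fixed millimetre grid is less useful, because the article gives no VAS SD from which to set it. If the SD were 20 to 25 mm (assumption), the margin in Step 4 would be 0.218 × 20 = 4.4 mm to 0.218 × 25 = 5.5 mm. A 20 mm shift with 15% of one arm missing moves the contrast only 0.15 × 20 = 3 mm, so a grid ending at 20 mm could stop short. If no shift that fits on the 100 mm scale changes the conclusion, report that.

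In Stopping rules, separate the end of trial treatment from the end of data collection: VAS, EQ-5D-5L and cost outcomes will be sought from every participant who has not withdrawn consent. This does not alter who stops treatment.

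The cost is slightly more analysis in the SAS package already planned, a few more questionnaires, and scenarios that may look less favourable.
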